### Screening for participation and randomization

Participants are selected by the study investigators from patients referred to the regional cLBP network. When a patient is referred to the regional cLBP network, the rehabilitation physician screens information provided by the referring general practitioner or medical specialist before referring him to the multidisciplinary cLBP clinic. Each patient undergoes a standardized multidisciplinary evaluation including a medical examination, psychological, social and occupational interviews and self-administered questionnaires. The rehabilitation physician verifies whether an extensive physical examination and imaging or laboratory studies according the guidelines [24] have been performed if necessary. The rehabilitation physician explains the study procedure and, if someone meets the inclusion criteria and has none of the exclusion criteria, asks the patient to sign the informed consent form. After signing, one of the three treatment strategies is randomly allocated to each patient.

The randomization procedure of participants is determined by a computer randomization feature which automatically allocates the patient to one of the treatment strategies. This system has been described in previous studies [16,17,22]. An independent research assistant prepares envelopes and numbers them sequentially according to the randomization list. Envelopes are given to the rehabilitation physician who opens them at the end of the clinical evaluations described above.

### Interventions

The three treatment strategies last 5 weeks but the treatment content of each strategy is different. FRP involves 6 hours of treatment a day, 5 days a week in group of 6 to 8 patients. AIP includes individual rehabilitation with a private physiotherapist for 1 hour 3 times a week and individual exercises to be performed at home twice a week for 50 minutes. The mixed strategy includes AIP combined with 5 one-day group sessions. Patients are off work during the 5 weeks of treatment in all three groups.

#### Functional restoration program (FRP)

The group performs exercises supervised by a physiotherapist who adjusts the exercise intensity to each participant every week. During the first week, patients learn muscular warm-up and stretching techniques, improve their flexibility, and perform cardio-respiratory exercises. During the second week, patients begin muscular-strengthening exercises. During the third week, muscular strengthening increases with endurance exercises. Patients perform weightlifting as well as proprioception and coordination exercises. In the fourth and fifth weeks, the intensity of strengthening exercises increases progressively. The endurance training is adapted to each patient’s heart rate and to the exercise stress test performed before the program. Patients perform work simulations during occupational therapy sessions.

Strengthening exercises are performed exclusively with isotonic techniques. Proprioception is developed with static and dynamic destabilization exercises. Walking, running, and cycling develop cardio-respiratory endurance.

Each week, patients attend a clinic with the rehabilitation specialist who supervises the program. They are referred to the psychologist at least once in the first week and for further treatment if requested. Dietary advice is given. The schedule of interventions is standardized for all patients (Additional file 1).

#### Ambulatory individual physiotherapy (AIP)

Each individual session lasts 1 hour and includes only active exercises supervised directly by a private physiotherapist of the regional cLBP network. All private physiotherapists participate in an information session and agree to apply the program as described. During the first 2 weeks, the program includes flexibility training and pain management, stretching, and proprioception exercises. Patients continue these exercises during the third and fourth weeks and start muscular strengthening. The last week focuses on functional exercises and endurance training. The program includes 50 minutes of individual home exercises 2 days a week (these can include stretching, jogging and swimming). This part of the program is agreed upon by the patient and physiotherapist and depends on the facilities available. It is not standardized. All exercises are isotonic, and no specific equipment is required or provided. The cardio-respiratory exercise training should be based on 70% of the theoretical maximum heart rate: patients should therefore monitor their heart rate during exercises. At the beginning of the program, patients sign an agreement to follow the prescribed exercises. Patients have to record the duration, type, and number of exercises performed at home.

#### Concomitant treatments

All other treatments are allowed, except for the following: physiotherapy other than AIP in the cLBP regional network, other manual techniques, surgery for back pain, and hospitalization for LBP. In the case of administration of any of these treatments, patients are eliminated from the study.

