#### Withdrawal criteria

A patient may leave the study at his own or an investigator’s initiative. The exclusion criteria are expected to extent to withdrawal of consent for participation, development of a criterion for non-inclusion or administration of a prohibited treatment during the 5 weeks’ course.

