#### Primary outcome measurement

The primary outcome of the trial is represented by the effectiveness of the impact of the mixed strategy on being able to work compared to FRP and AIP. Being fit for work is evaluated by the duration of sick leave in 1 year: the number of days’ sick leave during the preceding 12 months and during the 12 months of the study is collected for each patient and verified by checking with the health insurance provider.

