#### Analyses of efficacy

The effects of treatment conditions on the various outcomes will be compared using an “intention to treat” approach. Data analysis will be performed using SPSS 12.0 software. The significance level (p) has been defined as 0.05. Results will be expressed as mean ± standard deviation (for quantitative data) or percentage (for qualitative data). The initial comparability of the three groups will be verified by ANOVA or Kruskal-Wallis test (if necessary) for quantitative data, and t test for qualitative data. Between groups quantitative data will be compared by Student’s test and qualitative data by Pearson χ2 test or Ficher’s exact test for small samples. Changes within groups will be assessed by t test and MacNemar χ2 for paired data for quantitative and qualitative data, respectively. There will be a post-hoc analysis of the dropout group and missing values. Patient characteristics of the dropouts will be compared to those of the group that complete each treatment.

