#### Economic analyses

The health-care costs of each treatment will be evaluated and the cost of each of the three strategies will be compared from the point of view of health insurance, i.e. the payer: sick leave costs will be estimated according to reimbursement of health insurance; costs of hospitalizations and drugs will be assessed using their basic tariffs; costs of medical and paramedical consultations and additional tests will be assessed using the basic tariffs for hospitals and fees for independent practitioners. Costs of each treatment will be evaluated from the point of view of health insurance.

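### Eliminating randomised patients who receive a prohibited treatment conflicts with the promised intention-to-treat analysis, and two sections give different time windows for the rule

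*Protocol article*

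**What the plan says.** Three sections of the protocol article bear on the same patients.

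- **Concomitant treatments** lists what is not allowed: "physiotherapy other than AIP in the cLBP regional network, other manual techniques, surgery for back pain, and hospitalization for LBP". It then says: "In the case of administration of any of these treatments, patients are eliminated from the study". It gives no period.
- **Withdrawal criteria** names, besides withdrawal of consent, "development of a criterion for non-inclusion or administration of a prohibited treatment during the 5 weeks" of the course.
- **Analyses of efficacy** says that the effects on the various outcomes "will be compared using an “intention to treat” approach". It adds a post-hoc analysis of dropouts and missing values.

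Two further parts matter for the consequences. Under **Primary outcome measurement**, days of sick leave over the 12 months are collected for every patient and "verified by checking with the health insurance provider". Under **Cost analysis**, patient diaries record all hospitalisations and paramedical care up to 1 year, and **Economic analyses** states that "costs of hospitalizations and drugs will be assessed using their basic tariffs".

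**The concern.** Intention to treat means that each randomised patient is analysed in the assigned arm, whatever care follows. A rule that removes patients for care received after randomisation does the opposite. The removal may also be informative, because back surgery and hospitalisation for low back pain are plausible markers of a poor course, and the primary outcome is sick leave over the following year. If such patients leave the analysis, and do so at different rates or with different prognoses by arm, the comparison of sick leave is no longer protected by randomisation.

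The cost comparison is exposed too. If the rule has no time limit, patients hospitalised for low back pain at any point drop out of an analysis that sets out to count hospitalisations.

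With conflicting rules in print, who enters the primary analysis could be settled after outcomes are known.

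**Working it through.** **Step 1: whom does each rule reach?** The year after randomisation has three periods: the wait before treatment (up to 90 days, section Inclusion), the 5-week course, and the rest of the 12-month follow-up.

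| Section | Wait | 5-week course | Later follow-up |
|---|---|---|---|
| Concomitant treatments, as worded | eliminated | eliminated | eliminated |
| Withdrawal criteria | not covered | withdrawn | not covered |
| Analyses of efficacy (intention to treat) | kept in analysis | kept in analysis | kept in analysis |

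The first two rows disagree in two of the three periods. Either of them disagrees with the third row at least during the 5-week course. Choosing the narrower window therefore reduces the conflict without removing it: a patient eliminated in week 3 would still have no 12-month outcome.

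**Step 2: does any section keep these patients?** Sick leave could be recovered through the insurer check. The SF-36 and the Dallas Pain Questionnaire are collected at the assessments, and the diary is handed in at the follow-up appointments (Observational follow-up, Cost analysis), so these need continued attendance. No section says that eliminated patients continue to attend. Equally, no section says in words that their data are left out of the analysis.

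**Step 3: how large could the bias be?** The plan gives no elimination figure to reproduce. The yardstick is the 30-day difference under Sample size. Let p be the share eliminated in an arm, and E the mean excess sick-leave days of those eliminated over those retained. The full arm mean equals the retained mean plus p × E. The bias in the difference between arms A and B is therefore

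p_A × E_A − p_B × E_B.

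Neither p nor E is in the document. The values below are assumptions, with E equal in both arms and ranging from 60 to 180 days:

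| p_A v p_B | Difference | Bias, E = 60 | Bias, E = 180 |
|---|---|---|---|
| 5% v 5% | 0.00 | 0 days | 0 days |
| 5% v 2% | 0.03 | 1.8 days | 5.4 days |
| 10% v 3% | 0.07 | 4.2 days | 12.6 days |
| 15% v 5% | 0.10 | 6 days | 18 days |

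The last value is 18/30 = 60% of the target difference. Equal shares do not guarantee zero bias. With 5% eliminated in each arm, but E of 180 days in one and 60 in the other, the bias is 0.05 × (180 − 60) = 6 days. The sign depends on which arm loses more, or worse, patients.

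**The case against.** The best defence is to read the two rules together. Concomitant treatments stands under Interventions, and the interventions last 5 weeks, so it may say what is prohibited while Withdrawal criteria says when. The diaries support this, since they go on recording hospitalisations and paramedical care at 6 months and 1 year. On that reading most surgery and hospitalisation in the year would trigger nothing, the cost conflict largely shrinks, and only the patients removed during the course remain affected. This is a fair reading and it limits the harm. But one section has to be read into the other to reach it, and it still removes randomised patients for a post-randomisation event.

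A second defence is that elimination may mean leaving treatment only, with sick leave still obtained from the insurer. That is possible, but the stated object of the elimination is the study, and no sentence supports the softer meaning.

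Several stronger conclusions are tempting, and the document does not support them:

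- *The worst outcomes are removed from the primary and cost analyses.* This is an inference. The article never says the data are dropped, and other physiotherapy or manual techniques need not mark a poor outcome.
- *The rule works unevenly by arm because network physiotherapy is exempt.* The rule is worded alike for all arms, and no figures on outside care are given.
- *Exclusion pulls the mixed strategy and FRP together.* It could narrow, widen or leave unchanged that difference.
- *Power falls by a stated amount.* The article gives no standard deviation, and Sample size already allows for 10% dropout, so no power figure can be charged to this rule.
- *The plan has no proper handling of losses.* It announces an analysis of missing values, and further detail may sit in a fuller document.

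**Conclusion.** The contradiction is established from the text alone. The elimination rule, under either window, cannot be followed together with intention to treat, and the two windows differ. The rule bears on who enters the primary analysis, so it needs to be settled before the data are analysed.

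The bias is a possibility of unknown size and direction. It requires that elimination, or its link to sick leave, differ by arm, and it may be zero. The 0 to 18 days shown rest wholly on assumed shares and excess days, and the upper values are harder to credit if the trigger is confined to the 5 weeks. The loss of hospitalisation costs for low back pain is material mainly on the reading without a time limit.

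**What to change.** 1. Reconcile Concomitant treatments with Withdrawal criteria so that one period is stated, including whether the wait before treatment counts. Which period applies is for the trial team to decide.
2. Separate stopping the assigned programme from leaving the study.
3. State that all randomised patients who have not withdrawn consent to data use stay in follow-up and in the sick-leave and cost analyses under their assigned arm, whatever other care they receive.
4. Obtain 12-month sick leave for these patients through the insurer verification already planned.
5. Record prohibited treatments as protocol deviations, and confine any exclusion on that ground to a sensitivity analysis.

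This costs a few sentences and the continuation of visits and insurer checks that are already scheduled. The list of prohibited treatments is unchanged. The downside is that the intention-to-treat effect may look smaller than one computed without these patients.

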### Outcome measurement

Standardized questionnaires are used to measure the primary and secondary outcomes. Our choice of outcome evaluation methods is based on two previous trials conducted by our working group to evaluate the effectiveness of various interventions in the management of cLBP [16,17,22]. They are also in line with international recommendations.

#### Primary outcome measurement

The primary outcome of the trial is represented by the effectiveness of the impact of the mixed strategy on being able to work compared to FRP and AIP. Being fit for work is evaluated by the duration of sick leave in 1 year: the number of days’ sick leave during the preceding 12 months and during the 12 months of the study is collected for each patient and verified by checking with the health insurance provider.

#### Secondary outcome measurement

The secondary outcome of the trial is represented by the impact of the mixed strategy on quality of life and social ability compared to FRP and AIP. Quality of life and social ability are evaluated by the Short Form Health Survey questionnaire (SF-36) and the Dallas Pain Questionnaire (DPQ).

- The SF-36 is a self-administered questionnaire used to assess quality of life related to health [25,26]. This tool consists of 36 items grouped into eight dimensions, each corresponding to a different aspect of health: Physical Functioning; Role Limitations due to physical problems; Bodily Pain; General Health perceptions; Energy/Vitality; Social Functioning; Role Limitations due to emotional problems; and Mental Health. These 36 items allow evaluation with two summary scores: Physical and Mental Health Component Summary Scores (assessed by a score between 0 and 100, with higher scores indicating better quality of life).

- the Dallas Pain Questionnaire (DPQ) [27,28] is a self-administered questionnaire used to assess the amount of cLBP that affects four aspects (daily and work-leisure activities, anxiety-depression, and social interest) of patients’ lives. These four aspects are scored from 0 to 100% (higher scores indicating poorer quality of life).

#### Complementary outcome measurement

Criteria evaluating impairments and activity limitations, personal beliefs and environmental conditions are collected because they can be explanatory factors of the primary and secondary criteria [29-39]. They are not endpoints of treatment strategies. All these complementary outcome measurements are shown in Table 1.

**Table 1 T1:** Complementary outcome measures

**Outcomes**	**Criteria**	**Tools**
Impairments and activity limitations	Pain	Visual analog scale [32,34]
	Trunk flexibility	Finger-floor distance [31]
	Trunk muscles endurance	Time of isometric contraction of the flexor muscles of the spine: Ito-test [33]
		Time of isometric contraction of the extensors muscles of the spine: Sorensen-test [30]
	Loading capacity	PILE-test (Progressive Isoinertial Lifting Evaluation) [35,36]
	Anxiety and depression	Hospital Anxiety and Depression scale [38].
Personal beliefs and environmental conditions	Patient’s fears and beliefs for physical activity by	Fear Avoidance Beliefs Questionnaire [37]
	Evaluation of the job constrain	Work Ability Index questionnaire (WAI) [39]

#### Cost analysis

Treatment costs and additional expenses are assessed from the point of view of the health insurance organisation which is paying. This is done in 3 ways:

- a “patient diary” is given to the patient at each follow-up appointment. The patient is asked to note all sickness absences in this diary whether related to cLBP or not, all hospitalizations, medical consultations, investigations, medical treatments and paramedic treatment. This diary is collected by the investigator at each follow-up appointment (end of treatment, 6 months and 1 year).

- the general practitioner is asked to complete and check the filling in the “patient diary”.

- the quality of the health economic data is randomly monitored for 20% of study participants. A request has been made to the each health insurance organization to have repayments continue during each patient’s participation in the study.

#### Compliance with treatment strategies

To verify patient compliance with the treatment management, private physiotherapists participating in the study, general practitioners and institutional therapists report any major difference from the study protocol to the investigators of the study.

### Assessment and procedures

The accuracy and completeness of the data collected is checked weekly by an independent research assistant to provide a suitable level of quality for the study. In particular, controls review the quality and completeness of outcomes, treatment execution and monitoring modalities, the dropout rate, and correct respect of application of enrolment criteria.

#### Inclusion

Inclusion of patients is decided during the multidisciplinary cLBP clinic described above. All patients satisfying inclusion and non-inclusion criteria are offered the possibility to take part in the study. The inclusion appointment includes: verification of inclusion and non-inclusion criteria, information to the patient about the study and signing of informed consent for participation in the study by the patient. Once consent for participation has been signed, the participant is then randomized and allocated to one of the three treatment arms. The treatment strategy is then implemented within the next 90 days and the patient’s schedule is decided (date of initial assessment, appointment dates corresponding to the allowed treatment strategy). Participants are off work for the 5 weeks of treatment.

#### Observational follow-up

Assessments are undertaken in the rehabilitation center by an independent physiotherapist. Four stages of participant assessment are planned in this RCT (Figure 1):

- initial (T0) and end of treatment (T5w) assessments are performed during the seven days preceding the treatment and on the last day of treatment, respectively. These assessments include personal data, medical history, intensity of pain on the VAS, FFD, Ito, Sorensen and PILE tests, DPQ, FABQ, SF-36, HAD and WAI questionnaires.

- follow-up assessments are performed at 6 months and 12 months during the follow-up period. These assessments include interviews and clinical examination, intensity of pain on the VAS, FFD, Ito, Sorensen and PILE tests, DPQ, FABQ, SF-36, HAD and WAI questionnaires, number of days’ sick leave, patient diary (medical and paramedical interventions).

### Adverse events

The study provides a direct benefit for each patient in that all patients receive standardized physiotherapy treatment which is consistent with international recommendations and has already been assessed in our previous studies. No specific adverse effects related to the study are expected for patients. Common adverse events associated with this kind of treatments are those injuries which might occur following the proposed activities, at the rehabilitation center, in the physiotherapist office, or related to transport. Any adverse events would be managed in accordance with current rules of good clinical practice. All adverse events will be reported to the regulatory authority and the Ethics Committee in accordance with relevant regulations.

### Analyses

#### Sample size

Based on the available literature [7-15] and following previous trials [16,17,22], we assume that a difference of 30 days’ sick leave a year between treatment arms is clinically significant. With a sample size of 60 patients in each treatment arm, accepting an alpha error of 0.05 and a power of 0.80, it is possible to measure a minimum difference of 30 days’ sick leave during the subsequent 12 months’ treatment. To compensate for an estimated 10% dropout rate, a total of 180 people will be included.

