**Methods/Design:**

This paper describes the protocol for a prospective, randomized, controlled, clinical trial in working aged patients with cLBP. Three treatment strategies are compared: (1) intensive and multidisciplinary program conducted in a rehabilitation center; (2) less intensive outpatient program conducted by a private physiotherapist; (3) mixed strategy combining the same out program with a multidisciplinary intervention. The primary outcome of the trial is the impact of the mixed strategy on being able to work compared to hospital centered-program and out program. The secondary outcome is the impact of the mixed strategy on quality of life and social ability compared to the two others programs. The intervention part of the trial programs will take 5 weeks and observational follow-up will take 12 months. The sample size will be 180 participants (60 for each arm). The project has been approved by the Ethical Committee of Angers Hospital, France.

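### Sample size: 60 per arm is both the number said to give 80% power and the number said to absorb 10% dropout, so as written there is no allowance

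*Protocol article*

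**What the plan says.** The Sample size section (under Analyses) makes two statements in succession.

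- The power statement: "With a sample size of 60 patients in each treatment arm, accepting an alpha error of 0.05 and a power of 0.80", the trial can detect a minimum difference of 30 days of sick leave over the 12 months. The target is justified by the assumption that "a difference of 30 days’ sick leave a year between treatment arms is clinically significant".
- The dropout statement: "To compensate for an estimated 10% dropout rate, a total of 180 people will be included".

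The Methods/Design part of the abstract confirms that 180 is three arms of 60. No smaller evaluable number per arm appears anywhere in the article. The planned comparison of quantitative outcomes is in Analyses of efficacy: "Between groups quantitative data will be compared by Student"'s test, at a significance level of 0.05.

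**The concern.** A dropout allowance is the gap between the number that must be analysed and the number enrolled. Here the two are the same number, so the text claims a compensation that its own figures do not contain.

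This section is the only justification the article gives for the trial's size. If 60 is the number that must be analysed, the 80% applies only when nobody is lost, and the plan itself expects to lose one patient in ten. Readers would then credit the trial with somewhat more power, and a slightly smaller detectable difference, than it has under its own assumption.

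**Working it through.** **Inputs, all from the Sample size section unless noted**

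- Alpha 0.05. Sidedness is not stated; two-sided is assumed and the alternative is shown.
- Power 0.80, difference 30 days, 60 per arm, dropout 10%, total 180.
- Test: Student's test (Analyses of efficacy).
- Standard deviation: not given. The 60 per arm therefore cannot be reproduced independently, and the 80% at 60 is taken as stated. The steps below do not need the standard deviation.

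**1. Size of the allowance**

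3 × 60 = 180, and 180 − 180 = 0 patients.

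**2. What a 10% allowance on 60 would require**

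60/(1 − 0.10) = 66.7, so 67 per arm and 3 × 67 = 201 in total. The cruder 60 × 1.10 = 66 per arm gives 198. Neither is 180.

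**3. Power after dropout, taking the text at its word**

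- Evaluable per arm: 60 × 0.90 = 54.
- At 60 per arm and 80% power, the standardised signal is 1.960 + 0.8416 = 2.8016 (normal approximation).
- The signal scales with √n, so at 54 it is 2.8016 × √(54/60) = 2.8016 × 0.9487 = 2.658.
- Power = Φ(2.658 − 1.960) = Φ(0.698) = 0.757.
- The noncentral t gives the same 75.7%. A one-sided 0.05 test gives 76.2%, and a three-arm one-way ANOVA gives 75.3%.

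**4. Difference detectable with 80% power at 54 per arm**

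- Normal approximation: 30 × √(60/54) = 31.6 days.
- t-test: the standardised difference needed is 0.5157 at 60 per arm and 0.5441 at 54, so 30 × 0.5441/0.5157 = 31.65, or about 31.7 days.

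**5. The other reading: 54 evaluable was the powered number**

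- 54/0.90 = 60 exactly, so 60 per arm would already include the allowance.
- Power with all 60 analysed: 2.8016 × √(60/54) = 2.953, and Φ(2.953 − 1.960) = Φ(0.993) = 0.840. The noncentral t also gives 84.0%.
- Power after 10% dropout is then 80%, as intended.

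| Reading | Power at 60 per arm | Power at 54 per arm | Sentence that is wrong |
|---|---|---|---|
| 60 evaluable needed (as written) | 80% | about 76% | the dropout statement |
| 54 evaluable needed | about 84% | 80% | the power statement |

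**The case against.** The strongest reply is that 54/0.9 is exactly 60, so the planners may have started from 54 and inflated correctly. A reader might infer from the text that the trial fails to deliver its stated power. The document does not support that as a fact: under this reading the power is intact and only the wording is at fault. This part of the objection stands, and it limits the conclusion to an inconsistency whose effect on power depends on the reading. It does not remove the inconsistency, because 54 appears nowhere and the 0.80 is attached explicitly to 60.

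A second reply is that dropouts may still have a primary outcome. Primary outcome measurement says sick leave is checked with the health insurance provider, and Analyses of efficacy plans an intention-to-treat approach. That may reduce the real loss. But the sample size section itself budgets for 10%, Concomitant treatments removes patients who receive a prohibited treatment, and the article does not say that outcomes will be obtained for those who leave.

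Two further inferences should be resisted.

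- Back-solving gives a standard deviation of about 58 days (two-sided t-test, 60 evaluable) or about 55 (54 evaluable). Neither is the sponsor's planning value. Its absence from a condensed article is not itself a fault, and power losses computed from larger assumed values would have nothing to do with dropout.
- The article's Hypothesis section expects no significant difference between the functional restoration program and the mixed strategy, so lower power might seem to favour that result materially. At a true 30-day difference, the chance of a non-significant result rises only from 20% to about 24%. Reading non-significance as sameness is a separate question.

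**Conclusion.** The point holds as an internal contradiction: the same 60 per arm cannot be both the number that yields 80% power and the number inflated for 10% dropout. On the text as written, power after the planned loss is about 76% for 30 days, or 80% for about 31.7 days. On the alternative reading, 80% holds after dropout and the power statement should refer to 54. Nothing in the article decides between them.

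The importance is modest: about 4 points of power and 1.7 days on a 30-day target, and possibly a matter of wording only. The figures assume a two-sided 0.05 test, equal arms, and loss of the primary outcome in exactly 10% of each arm. They do not depend on a standard deviation.

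**What to change.** State the evaluable number per arm and correct whichever sentence is wrong, using the standard deviation the sponsor actually planned with and not a back-solved one. One of these two statements would do:

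- If 60 was the powered number: 180 patients are randomised (60 per arm); after 10% dropout 54 per arm remain, giving about 76% power for 30 days, or 80% for about 31.7 days.
- If 54 was the powered number: 54 evaluable patients per arm give 80% power for 30 days; 60 per arm are randomised to allow for 10% dropout.

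No extra enrolment is asked for. The cost is a change of text; under the first option a stated figure becomes slightly less favourable. Trial status reports that data collection was ongoing and analysis still to come, so the correction could be made before results were known.
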